## Abstract

**Background:**

The HIV epidemic continues to disproportionately burden marginalized populations despite the availability of effective preventive and therapeutic interventions. Transgender women are severely affected by HIV worldwide including in Brazil and other low- and middle-income countries, with evidence of increasing new infections among young people. There is an urgent need for youth-specific HIV prevention and care interventions for young transgender women in Brazil.

**Objective:**

This study aims to (1) address stigma in the Brazilian public health system and (2) reduce barriers to HIV care and prevention with systems navigation among young transgender women aged 18-24 years in Rio de Janeiro, Brazil.

**Methods:**

The *Brilhar e Transcender* (BeT) study is a status-neutral, peer-led, single-arm digital intervention study enrolling 150 young transgender women in Rio de Janeiro, Brazil. The intervention was pilot tested and refined using data from a formative phase. The BeT intervention takes place over 3 months, is delivered remotely via mobile phone and in person by peers, and comprises three components: (1) BeT sessions, (2) digital interactions, and (3) automated messages. Eligibility criteria include identifying as transgender women, being aged 18-24 years, speaking in Portuguese, and living in the Rio de Janeiro metropolitan area in Brazil. The primary outcomes are HIV incidence, pre-exposure prophylaxis uptake, linkage to HIV care, and viral suppression. Primary outcomes were assessed at baseline and quarterly for 12 months. Participants respond to interviewer-based surveys and receive tests for HIV and sexually transmitted infections.

**Results:**

The study has been approved by the Brazilian and the US local institutional review boards in accordance with all applicable regulations. Study recruitment began in February 2022 and was completed in early July 2022. Plans are to complete the follow-up assessment of study participants on July 2023, analyze the study data, and disseminate intervention results by December 2023.

**Conclusions:**

Interventions to engage a new generation of transgender women in HIV prevention and care are needed to curb the epidemic. The BeT study will evaluate a digital peer-led intervention for young transgender women in Brazil, which builds on ways young people engage in systems and uses peer-led support to empower transgender youth in self-care and health promotion. A promising evaluation of the BeT intervention may lead to the availability of this rapidly scalable status-neutral HIV intervention that can be translated throughout Brazil and other low- and middle-income countries for young transgender women at high risk of or living with HIV.

**Trial Registration:**

ClinicalTrials.gov NCT05299645; https://clinicaltrials.gov/ct2/show/NCT05299645

**International Registered Report Identifier (IRRID):**

DERR1-10.2196/44157

## Introduction

Efforts to end the HIV epidemic by 2030 will not be possible without enhanced efforts to prevent new infections among youths and young adults [1]. Despite the availability of effective HIV care and prevention interventions, reductions in HIV prevalence have stalled, in part, owing to the lack of progress in reducing new infections among youths, especially those in low- and middle-income countries (LMICs) where most new infections are acquired. Innovations in HIV interventions have also failed to adequately reach marginalized populations most affected by HIV [2]. Transgender women are one of the most severely affected populations by HIV worldwide [3]. Brazil has a concentrated HIV epidemic with a 0.4% prevalence in the general population [4] with over 900,000 people living with HIV in the country [5] and the highest prevalence among transgender women who have sex with men [6,7]. Within the population of transgender women, young transgender women are at high risk for HIV and poor HIV care outcomes. The first respondent-driven sampling-based study of HIV risk and pre-exposure prophylaxis (PrEP) awareness among Brazilian transgender women identified that 24.2% of youths aged 18-24 years were living with HIV. Young transgender women also had lower knowledge of HIV prevention strategies (including PrEP) and higher HIV risk than their older peers, with 3 times as many unrecognized infections than adults [8]. These findings are worse than those reported in prior research, suggesting that 1 in 5 young transgender women were infected with HIV before having been aged 25 years [9,10].

Global data reflect a lack of incident infection decline among youths and point to a need for early intervention to curb risk among young transgender women [11]. In a study conducted from 2018 to 2020 using the Limiting Avidity assay as part of a recent infection testing algorithm, the annualized HIV incidence rate was 7% overall and 9% among transgender women [12]. In the largest PrEP demonstration study in Latin America, which enrolled a total of 9509 people, young and transgender participants had lower odds of long-term engagement in PrEP [13].

The Brazilian Public Health System (Sistema Único de Saúde) ensures universal and equitable provision of health care to the whole population; their approach toward the HIV epidemic was human rights–based and science-driven, integrating both prevention and treatment efforts into the Brazilian universal health care system and including a fundamental role of social movements advocacy. Brazilian regulations guide public health services to use social names (ie, names that transgender people use that are different from what is on their government-issued identification) and requested pronouns for them. Despite these protections, discrimination toward transgender people in the Brazilian Public Health System is well documented. For young transgender people, discrimination exacerbates common youth-related barriers to HIV prevention and care. Previous Brazilian research identified stigma as a critical roadblock to HIV prevention and care for transgender women [14,15]. Much like research from the United States, transgender women in our Brazilian study reported experiencing antitransgender stigma in the health care system [6,16-19], and most attributed their underuse of medical care to stigma [6,14]. Transgender people are known to postponing necessary care owing to experiences of and anticipation of discrimination [20,21]. Low health care usage may be the reason underlying very low awareness of PrEP in our US-based research with young transgender women [22]. Young transgender women face the challenge of addressing medical needs related to their gender identity, which compounds typical adolescent development [9,23-25]. For youths, health literacy, systems navigation, and low risk perception are barriers to HIV testing and linkage to HIV care [26-28].

The lack of interventions among young transgender women presents a troubling outlook to the HIV epidemic for young Brazilian transgender women. Overall, most interventions with transgender women focused on those already living with HIV [29]. The few primary prevention interventions are limited to pilot studies of small group sessions that combine didactic and participatory learning, with no information gathered on HIV incidence and risk behavior. Only one intervention has been developed and has shown efficacy for increasing HIV-related preventive behavior among young transgender women [30]. No known interventions have been developed to increase HIV care outcomes among young transgender women. Our data point to an urgent need for youth-specific HIV prevention and care interventions for young transgender women in Brazil. To address limitations in availability of HIV prevention and care interventions for young transgender women, we designed the *Brilhar e Transcender* (BeT [“shine and transcend” in English]) study, which combines a social marketing campaign to address antitransgender stigma in health services toward transgender women and an adapted evidence-based, HIV status–neutral intervention that uses peer-led digital and in-person systems navigation. Our primary aims are to (1) address stigma in the Brazilian public health system, (2) intervene to overcome youth challenges with health care systems navigation, and (3) implement our intervention among young transgender women aged 18-24 years in Rio de Janeiro, Brazil.

## Methods

### Study Design

The BeT study is one of 8 sponsored research projects chosen to be a part of a Eunice Kennedy Shriver National Institute of Child Health and Human Development–funded Prevention and Treatment through a Comprehensive Care Continuum for HIV-affected Adolescents in Resource Constrained Settings (PATC^3^H) consortium [31], which conducts clinical research and evaluation of a variety of combination interventions to improve health outcomes among adolescents at risk for HIV and youths living with HIV in resource-limited settings. The BeT study is the only PATC^3^H project conducted in Latin America and among transgender youths and builds on decades of research and community engagement with transgender communities. The BeT study is a peer-led, digital-based intervention study aiming to enroll 150 young transgender women in Rio de Janeiro, Brazil.

### Eligibility Criteria

Inclusion criteria are (1) having been assigned the male sex at birth and self-identifying as *travesti*, a transgender woman, or having a gender identity different from identities typically associated with the assigned sex at birth; (2) being aged between 18 and 24 years; (3) providing consent for study participation; (4) living in Rio de Janeiro or the greater metropolitan area; and (5) being sexually active. Additional criteria for HIV-negative individuals include (1) no current PrEP use, (2) PrEP indication per Brazilian standards of care, and (3) no PrEP contraindication. For participants living with HIV, additional inclusion criteria are (1) having a confirmed HIV diagnosis, (2) not currently using antiretroviral therapy (ART) or having a detectable viral load and treatment that is not linked to HIV care.

Exclusion criteria include participation in any HIV prevention or care intervention study in the last year, refusal to undergo HIV testing, or having any health condition that, in the opinion of the investigator, precludes participation in the study or may lead to harm to the participant.

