**Substance use**			
	Alcohol Use Disorders Identification Test for alcohol consumption (3 items)	Baseline and quarterly	Bush et al [36]
	Alcohol, Smoking and Substance Involvement Screening Test	Baseline and quarterly	World Health Organization [37]
Stigma and discrimination (including transgender-specific health care discrimination)		Baseline and quarterly	Grinsztejn et al [6], Costa et al [15], and Scandurra et al [38]
Violence		Baseline and quarterly	Grinsztejn et al [6]
Overall health issues		Baseline and quarterly	Grinsztejn et al [6]
Medical mistrust (12-item Group-Based Medical Mistrust Scale)		Baseline and quarterly	Adapted from Thompson et al [39]
Medical avoidance		Baseline and quarterly	Adapted from James et al [40]
HIV knowledge and attitudes (10-item HIV Knowledge Questionnaire adapted to 8 items, HIV testing and counseling attitudes and knowledge)		Baseline and quarterly	Oglesby and Alemagno [41] and Kalichman and Simbayi [42]
Self-efficacy			Adapted from Zhao et al [43]
HIV testing, prevention, and care		Baseline and quarterly	Grinsztejn et al [6]
HIV perceived risk index		Baseline and quarterly	Lauby et al [44]
Testing and diagnosis of sexually transmitted infections		Baseline and quarterly	Grinsztejn et al [6]
Adherence (adapted to antiretroviral therapy and pre-exposure prophylaxis)		Baseline and quarterly	Adapted from Wilson et al [45]
Overall mental health assessment and suicide		Baseline and quarterly	Grinsztejn et al [6] and Jalil et al [46]
The Patient Health Questionnaire for Depression and Anxiety scale		Baseline and quarterly	Kroenke et al [47]
The Primary Care Posttraumatic Stress Disorder scale		Baseline and quarterly	Prins et al [48]
Social support (Multidimensional Scale of Perceived Social Support)		Baseline and quarterly	Zimet et al [49]
Resilience (2-item Connor-Davidson Resilience scale)		Baseline and quarterly	Connor and Davidson [50]
Brazilian political context		Baseline and quarterly	The authors of this study
Sexual behavior		Baseline and quarterly	Adapted from Rocha et al [51]

**Table 2 table2:** Schedule of events of the *Brilhar e Transcender* study.

			Baseline		Week 12		Week 24		Week 36		Week 48 or early termination^a^		HIV seroconversion visit
Eligibility			✓										

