We will also assess outcomes comparing data from the external comparison group to the BeT intervention group. First, we will conduct sensitivity analyses to compare the demographics of our intervention group to those of the external comparison group. In the analysis, we will focus on comparisons between the BeT intervention group and the external comparison group on measures of PrEP and ART adherence and viral suppression. Primary analyses will involve intention-to-treat analysis without considering adherence to the BeT intervention. This analysis will be a comparison of initiators of PrEP and ART, and we shall adjust for baseline confounders related to age or race. We have chosen to compare initiators of PrEP or ART and not assess PrEP uptake because a comparison of initiators parallels intention-to-treat analysis in which assignment and initiation of the treatment strategies occur together at baseline, regardless of whether individuals continue on the strategies after baseline [52]. We will combine outcome estimates with the cost estimates of the intervention component to calculate cost per participant and roughly estimate costs per HIV infection averted or poor health outcomes based on cohort data being collected in Brazil on HIV incidence and care outcomes.

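### The external comparison of PrEP and ART initiators omits treatment history from its stated adjustment, so a differing mix of new users, restarters and people already on ART would confound it

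*Protocol article*

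**What the plan says.** Under Statistical Analysis, the protocol article plans "comparisons between the BeT intervention group and the external comparison group on measures of PrEP and ART adherence and viral suppression". It fixes the population and the adjustment in one sentence: "This analysis will be a comparison of initiators of PrEP and ART, and we shall adjust for baseline confounders related to age or race". The reason given for choosing initiators is that "a comparison of initiators parallels intention-to-treat analysis in which assignment and initiation of the treatment strategies occur together at baseline". The term initiator is not defined, and the external group's entry criteria are not described.

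Under Eligibility Criteria, the PrEP rule opens with "Additional criteria for HIV-negative individuals include (1) no current PrEP use" and goes on to require that PrEP be indicated under national standards and not contraindicated. On the ART side, beyond a confirmed diagnosis, the rule is "not currently using antiretroviral therapy (ART) or having a detectable viral load and treatment that is not linked to HIV care". The only condition with a time window is "Exclusion criteria include participation in any HIV prevention or care intervention study in the last year".

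Table 1 lists a survey domain on HIV testing, prevention and care, and an adherence measure for ART and PrEP, both collected at baseline and quarterly. The individual items are not shown.

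**The concern.** Someone who stopped PrEP in routine care shortly before screening meets the entry rule just as someone who has never taken it does. If she resumes in the study, nothing stated in the article keeps her out of the initiator analysis. The same holds for lapsed ART users. The second ART route goes further, since it may bring in people who are on treatment at entry and so start nothing.

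Past use plausibly predicts the outcomes being compared: a person who has already lapsed once may adhere, or reach suppression, at a different rate from a first-time user. The stated adjustment does not include it.

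The article makes restarters a realistic group. The Introduction reports poorer long-term PrEP engagement among young and transgender participants in a large demonstration study, and recruitment takes place partly at the site's own HIV prevention services. It does not say how many there are.

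The study has a single arm, and the Discussion offers two answers to the lack of randomisation: before-after change and the external group. Confounding by treatment history would weaken the second.

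**Working it through.** No figure in the plan depends on this point, so there is none to reproduce. The check sets the entry rule against the analysis rule and then works out what a difference in mix would do.

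**Step 1. Who can be in the BeT group.**

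| Treatment history at entry | Admitted? | Starts treatment at entry? |
|---|---|---|
| Never used PrEP or ART | Yes | Can do |
| Used before in routine care, now stopped | Yes, no look-back stated | Can do, as a restart |
| Used before in an intervention study within the last year | No | Not applicable |
| On ART, detectable virus, not linked to care | Possibly, by the second ART route | No, already started |

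**Step 2. Which rows conflict with the stated rationale.** The rationale is that assignment and the start of treatment coincide.
- A new user who starts at entry satisfies it.
- A restarter who resumes at entry also satisfies it. What she adds is a history that may predict the outcome, which is confounding.
- A person already on ART does not satisfy it, because her treatment began before entry.

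**Step 3. Size of the confounding.** Let f_B and f_E be the restarter shares among BeT and external initiators. Let a_N and a_R be the outcome rates in new users and restarters, the same in both groups, so that BeT has no effect. Each group's rate is (1 − f)·a_N + f·a_R, so

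BeT minus external = −(f_B − f_E)·(a_N − a_R).

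The documents give none of these four quantities. The values below are assumptions chosen to show scale.

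- Worked case: a_N = 60%, a_R = 40%, f_E = 10%.
  - External: 0.9 × 60 + 0.1 × 40 = 58%.
  - BeT with f_B = 20%: 0.8 × 60 + 0.2 × 40 = 56%, a difference of −2 points.
  - BeT with f_B = 40%: 0.6 × 60 + 0.4 × 40 = 52%, a difference of −6 points.
- Range of absolute size, for shares 10 to 40 points apart and rates 10 to 30 points apart:
  - smallest: 0.10 × 0.10 = 1 point;
  - middle: 0.20 × 0.20 = 4 points;
  - largest: 0.40 × 0.30 = 12 points.
- If f_B = f_E the difference is 0. If the external group has more restarters, the sign reverses.

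For rough scale only, Sample Size and Power Calculation treats increases of 10 to 15 points in binary responses as detectable. That figure refers to within-person change, not to this between-group contrast.

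**Step 4. Does the same problem reach the before-after analysis?** No. That analysis compares baseline with follow-up in one cohort, so treatment history at entry is the same on both sides.

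**The case against.** The strongest objection is that the article is a condensed account. The definition of an initiator and a full covariate list may well be in a longer protocol or analysis plan, and their absence here is not a fault. That stands for the definition. It does not dispose of the point, because the article does state an adjustment, and that adjustment leaves out a plausible predictor of the outcomes in a population that the entry rule lets be mixed.

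Four stronger readings are tempting, and the documents do not support them:

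- *That the eligibility rule is wrong and needs a washout or a never-user condition.* Taking in people who have lapsed suits an intervention meant to link people to prevention and care. The fault lies in the external analysis.
- *That restarters break the alignment behind the initiator design.* They do not if they resume at entry. Only people already on treatment do.
- *That the external group is shown to be mixed, or that restarters will certainly be counted as initiators.* The external group's criteria are not given, and counting restarters is an inference from the lack of any stated exclusion. The one-year bar on intervention-study participants also removes some past users, though not those treated in routine care.
- *That PrEP uptake and care linkage are biased.* They are compared within one cohort, so fixed history does not bias them.

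It is also fair to object that the percentages above are assumed. They show that the effect could matter, not that it does.

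**Conclusion.** The point holds for the external comparison only. As stated, that analysis adjusts for age or race in a BeT group that may contain new users, restarters and, on the ART side, people who are not initiators. If the mix differs from the external group's, and past use predicts adherence or suppression beyond what age and race capture, the contrast is confounded by treatment history.

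Size and direction are unknown. The 1 to 12 point range rests wholly on the assumed shares and rates. It covers restarters only and does not quantify the effect of people already on ART. This is a weakness in the adjustment set that should be corrected before the comparison is run. It is not an error in who was enrolled.

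**What to change.** Leave eligibility unchanged and amend the external comparison under Statistical Analysis:

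1. Define an initiator by one rule and apply it to both groups.
2. Identify participants already on ART at entry and analyse them separately from ART initiators.
3. Add prior PrEP or ART use, coded never versus previous, to the adjustment set, taking it from the baseline survey on HIV prevention and care.
4. Where prior use is missing from either source, report a sensitivity analysis over a plausible range of restarter shares, using the formula above.

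Reporting first uptake apart from restart is optional description, not a correction.

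The cost is mainly analysis wording, but it depends on data. Table 1 names survey domains, not items, so the sponsor must confirm that past use was asked, and the external source must record it in a comparable way. Precision is a further limit on the ART side. If the 24.2% HIV prevalence cited in the Introduction applied to the 150 enrolled (an assumption, since entry criteria differ by HIV status), about 0.242 × 150 ≈ 36 participants would be living with HIV. One binary adjustment term is more realistic there than fine subgroups.

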### Formative Phase

The study had a formative phase, which comprised developing and implementing an antistigma campaign, and adaptation and pilot testing of the system navigation intervention [32]. The campaign content included information on basic gender definitions (sex, gender identity, gender expression, and sexual orientation), regulations linked to gender and sexual orientation minorities, the medical transition process, overview of mental health and hormone therapy among transgender people, transphobia and violence against transgender people, and HIV among transgender women (Figure 1). The antistigma campaign, focused on health care settings, clinical providers, and support staff, took place at 4 health clinics serving transgender women in Rio de Janeiro, Brazil. We collected pre- and postcampaign qualitative and quantitative data with providers (N=10) to assess whether antitransgender stigma beliefs and attitudes changed among providers and support staff.

We also conducted formative qualitative interviews with 10 young transgender women (mean age 22.2 years) to inform the development of the pilot intervention. The BeT study uses an effective US Centers for Disease Control and Prevention intervention called *Anti-Retroviral Treatment and Access to Services* for system navigation and linkage [33,34]. Three components of the intervention required adaptation: (1) content of the Anti-Retroviral Treatment and Access to Services intervention session plan and asynchronous interactions with young transgender women, (2) adaptation to the cultural context of Brazil, and (3) the digital interface. Ten young transgender women were recruited through community outreach by our community engagement specialists (n=2) and through referrals from other studies at Fiocruz (n=8).

The BeT study pilot-assessed the intervention’s preliminary efficacy among 20 participants. Results from the pilot intervention demonstrated preliminary efficacy for improving HIV prevention and care behaviors among young transgender women, as all HIV-negative participants were engaged in PrEP and all but one participant living with HIV became virally suppressed [32]. After the pilot phase, the team refined the intervention, which focused on streamlining the adapted intervention manual to improve peer navigator and participant accessibility. In addition, the team added additional medical monitoring to include important biomarkers of sexual health and HIV as part of the study protocol.

